### Statistical methods, data analysis

To investigate the effect of the intervention on self-reported use of rehabilitation aftercare at T3 (primary outcome), analysis of variance and related methods (analysis of covariance, regression analysis) will be used. We will conduct moderator analyses to examine the potential moderating role of variables (e.g., age, sex, health literacy level) and to analyze potential subgroups.

Descriptive analyses (means, standard deviations, correlation analyses) and qualitative analyses will be used to answer the secondary research questions.

IBM SPSS version 29 will be used for statistical analyses.

To assess potential dropout bias, we will perform subgroup analyses comparing complete datasets with those containing missing data. If the missing data shows to be Missing At Random (MAR), we plan to apply multiple imputation techniques to increase the statistical power and robustness of our analyses.

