#### Secondary research questions

2.Is the follow-up consultation associated with a better self-reported work ability four months after completion of MR?3.Is a structured follow-up consultation feasible as a low-threshold intervention in the GP practice?4.Can a structured follow-up consultation help to improve the level of information available to GPs on the subject of medical rehabilitation and rehabilitation aftercare?

The study will be conducted as a pragmatic cluster randomized crossover trial using a mixed-methods approach. Study participants will include medical rehabilitation patients and general practitioners. The study is conceived as a superiority trial where the intervention is tested against care-as-usual.

The study protocol was written in accordance with the Standard Protocol Items: Recommendations for Interventional Trials (SPIRIT) statement [35]; additional files 1 and 2.

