### Study design and data collection

#### Rehabilitation patients

In the first phase of the study, we will collect qualitative data in interviews with MR patients to evaluate comprehensibility and user-friendliness of the patient communication aid, which is intended to support study participants during the follow-up consultation with their GP. Participants will be presented with the draft version of the communication aid. In all sections, respondents will be asked to explain to what extent the individual items are comprehensible and whether there are any suggestions for rewording or other modifications. The procedure is based on the cognitive interview methodology and the “think aloud” method [43, 44].

In the second study phase, we will collect quantitative data (written questionnaires) in six inpatient rehabilitation centers in Northern Bavaria and neighboring regions. Questionnaire data will be collected longitudinally at three measurement points (T1: end of MR; T2: after follow-up consultation with GP (intervention group only; four to eight weeks after completion of MR); T3: four months after completion of MR).

The primary outcome is the self-reported utilization (initiation/continuation) of rehabilitation aftercare at T3 (four months post-rehabilitation). Self-reported work ability at T3 is assessed as a secondary outcome. We will collect additional variables to describe the sample and/or include them in moderator or predictive analyses. Table 1 summarizes the instruments used at each measurement point.

**Table 1 Tab1:** Instruments used in the study

Variable	Measure	T1 Completion of MR		T2 After follow-up consultation (IG only)		T3 4 months after completion of MR	
		IG	CG	IG	CG	IG	CG
Rehabilitation aftercare motivation, expectations	single items developed for this study	**X**	**X**				
Rehabilitation aftercare self-efficacy	single items developed for this study	**X**	**X**				
Rehabilitation aftercare recommendations by MR facility	single items developed for this study	**X**	**X**				
Evaluation of medical rehabilitation outcomes (subjective success of rehabilitation)	single items developed for this study	**X**	**X**				
Self-reported work ability	WAS [45, 46]	**X**	**X**				
Health-related quality of life	EQ-5D 5 L [47]	**X**	**X**				
Health literacy	HLS19-Q12-DE [48]	**X**	**X**				
Perceived communicative self-efficacy in patient-physician interactions	Single item developed for this study, based on Maly et al. [49]	**X**	**X**				

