#### General practitioners

To discuss a draft consultation guide for the intervention, we will collect qualitative data in interviews with GPs. The consultation guide serves as the basis for the structure of the interviews. No further structuring is used in order to obtain a broad range of feedback and comments, which will be incorporated into a revision of the guide.

We will collect quantitative data using a short online questionnaire that GPs will complete after each follow-up consultation. The questionnaire will assess the consideration and use of the rehabilitation discharge report for the consultation, the planning of further treatment and communication with the patient in this regard, as well as the evaluation of the aftercare recommendations of the rehabilitation facility.

Additionally, toward the end of the intervention and data collection, GPs will complete a one-time online survey to evaluate the intervention in summary. The online survey will assess the following variables:

Overall evaluation of the follow-up consultation (feasibility, motivation of patients).Use of the consultation guide (to check for treatment integrity), evaluation of the consultation guide.Evaluation of rehabilitation outcomes and effectiveness (in terms of “rehabilitation success”).Level of information and information needs regarding MR and rehabilitation aftercare.

We will develop items specifically for this purpose.

Figure 1 shows the data collection timeline.

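### Work ability, the only named secondary patient outcome, is assigned descriptive statistics only, with no planned between-condition estimate or interval; a lesser point is that GP information level is measured once, so measured improvement cannot be estimated

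*Protocol article*

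**What the plan says.** Under Secondary research questions, question 2 reads "Is the follow-up consultation associated with a better self-reported work ability four months after completion of MR". The same section describes the design: "The study is conceived as a superiority trial where the intervention is tested against care-as-usual". Under Study design and data collection, Rehabilitation patients, the outcome is given formal status: "Self-reported work ability at T3 is assessed as a secondary outcome". Table 1 lists "Self-reported work ability" (WAS) for the intervention and control groups at both T1 and T3. The text below the table describes it as a score from 0 to 10.

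Statistical methods, data analysis names analysis of variance, analysis of covariance and regression for the primary outcome. For everything secondary it says: "Descriptive analyses (means, standard deviations, correlation analyses) and qualitative analyses will be used to answer the secondary research questions".

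Question 4 asks: "Can a structured follow-up consultation help to improve the level of information available to GPs on the subject of medical rehabilitation and rehabilitation aftercare". The sample size section for general practitioners describes the same aim as a gain in knowledge. Information level appears only in the end-of-study survey: "GPs will complete a one-time online survey to evaluate the intervention in summary". The short questionnaire after each consultation covers use of the discharge report, treatment planning and communication, and the GP's view of the aftercare recommendations. The eligibility section restricts the quantitative GP evaluation to GPs who took part in the intervention.

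**The concern.** Question 2 compares two randomised conditions on a numeric score. Means and standard deviations by condition, plus correlations, describe that comparison but do not estimate it: no group difference with an interval is planned. The T1 score is available in both groups but has no stated role. It matters for more than precision, because clinic staff are not blinded to the current condition and a clinic coordinator approaches and recruits the patients, so the two conditions could differ at T1.

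At stake is whether the trial can say by how much work ability differs between conditions and how uncertain that is. The Aims section presents work ability as an indicator of effective rehabilitation, so readers will look for that number.

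Question 4 is a smaller matter of the same kind. Its wording asks about change, while the planned data give a level at one time point.

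**Working it through.** **Question and method side by side (question 2).**
- Question: work ability at T3, consultation against usual care.
- Data: WAS at T1 and T3, both groups.
- Stated method: means, standard deviations, correlations, qualitative analysis.
- Inferential methods: named in the preceding paragraph, for the primary outcome only.

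The data support a baseline-adjusted comparison, and the stated method stops short of one.

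**Do the planned numbers force a descriptive analysis?** Inputs from the Sample size section: six clinics, m = 29 per clinic and period, 6 × 29 = 174 per condition, ICC = 0.0195. The dropout chain reproduces: 348 / 0.80 = 435 and 435 / 0.65 = 669. Assumptions not in the document: two-sided alpha 0.05, cluster autocorrelation (CAC) 0.8 to 1, T1-T3 correlation r of 0, 0.5 or 0.7.

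The design effect is 1 + (m − 1)·ICC − m·ICC·CAC. It splits into an individual part, 1 − ICC = 0.9805, and a clinic-by-period part, m·ICC·(1 − CAC).
- CAC = 1: 0.9805 + 0 = 0.9805
- CAC = 0.8: 0.9805 + 29 × 0.0195 × 0.2 = 0.9805 + 0.1131 = 1.0936

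Adjusting for T1 WAS multiplies the individual part by (1 − r²). In SD units, SE = √(2 × [0.9805(1 − r²) + clinic-by-period part] / 174). The detectable difference at 80% power is 2.80 × SE (normal approximation).

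| r | Individual-level variance removed | Detectable, CAC = 1 | Detectable, CAC = 0.8 |
|---|---|---|---|
| 0 | 0% | 0.30 SD | 0.31 SD |
| 0.5 | 25% | 0.26 SD | 0.28 SD |
| 0.7 | 49% | 0.21 SD | 0.24 SD |

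**Degrees of freedom.** Six clinics by two periods give 12 cells. Subtracting 1 (intercept), 5 (clinic), 1 (period) and 1 (condition) leaves 12 − 8 = 4 for clinic-by-period variation. The 95% multiplier is then 2.78 rather than 1.96, so an interval resting fully on those 4 degrees of freedom is 2.78 / 1.96 = 1.42 times as wide. The normal-approximation figures in the table are therefore on the optimistic side.

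**Question 4.** The plan's figures reproduce: 348 × 3,050 / 13,805 = 76.9, so 77 GPs; 0.277 × 77 = 21.3, so 21 survey respondents. One measurement in 21 GPs gives a 95% interval for the mean level of ± 2.086 / √21 = ± 0.46 SD. That is an interval for the end level. A measured change needs an earlier value, and none is planned. If the same 21 GPs were measured twice, a paired comparison would detect about 2.80 / √21 = 0.61 SD of the change score at 80% power.

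**The case against.** The strongest reply is that the study calls itself exploratory, sizes only the primary outcome, and words question 2 as an association. Allocation is randomised, so means by condition already give a contrast, and correlation analyses are listed. The sentence also covers questions 3 and 4, for which descriptive and qualitative methods are suitable.

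Much of this stands, and it rules out four stronger readings.
- A reader might infer that question 2 cannot be answered at all. The documents do not support that: a crude contrast by condition would be available.
- A reader might infer that the plan discards the T1 score. It does not say so; it simply gives T1 WAS no stated use. Clinic and period terms are not spelled out for the primary outcome either, and an article may leave them to an analysis plan, so their absence is not the point here.
- A reader might convert r² into a gain of 1.3 to 2.0 times the sample size. The documents give no T1-T3 correlation, and the conversion treats patients as independent; more patients per clinic would not reduce clinic-by-period variation.
- A reader might infer that question 4 is unanswerable. The GP items are still to be written, so self-perceived change could be asked in the single survey, although the listed content is only level of information and information needs.

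What the reply does not remove is that the methods sentence makes no exception for question 2. It states a method rather than leaving one open. An exploratory outcome in a randomised comparison still calls for an estimate and an interval.

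**Conclusion.** The point holds in this limited form. As written, the only named secondary patient outcome would be reported as a crude contrast, without a planned between-condition estimate or confidence interval and without a stated role for T1 WAS. The primary outcome is not affected. The planned 174 per condition would support an adjusted comparison, with a detectable difference of roughly 0.21 to 0.28 SD for r between 0.5 and 0.7. That range is illustrative, since it rests on an assumed correlation, alpha and CAC and on a normal approximation that six clinics do not fully justify.

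Question 4 is a lesser point. Information level is measured once, afterwards, in intervening GPs only, so measured change cannot be estimated at any sample size; end level and perceived change can.

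**What to change.** **Question 2.** Take question 2 out of the descriptive sentence and state its analysis: a linear model of T3 WAS in all participants as allocated, whether or not they attended the consultation, with condition, T1 WAS, period and clinic, and allowing for clinic-by-period variation. Use a small-sample degrees-of-freedom correction because there are only six clinics. Report the adjusted difference in WAS points with its 95% CI. The cost is analysis wording only, with no new data.

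**Question 4.** The simpler course is to reword it to GPs' end-of-study information level and self-perceived change, and to write the survey items to match. If a paired change is wanted, collect the same items before each GP's first consultation. Items shown at first login to the project website would usually come too late, because the Recruitment section has GPs use that site to complete the questionnaire after a consultation. Report any change descriptively and do not attribute it to the intervention, since there are no comparison GPs. Rewording costs nothing beyond the item text; the earlier measurement adds a few items and a slight burden for GPs, and must be in place before consultations start.

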### Sample size

#### Rehabilitation patients

We expect an effect of the intervention on patients’ self-reported use of rehabilitation aftercare four months after they have completed MR (primary outcome). Specifically, we assume that more patients in the IG will use or continue to use aftercare services than patients in the CG. Since CG patients also receive follow-up recommendations from their MR facility, we expect a small effect in favor of the IG.

Utilization of the GPI aftercare programs (IRENA, other) is around 30% [3, 56], which can be used as a minimum approximation for the control condition. We assume an additional utilization rate of 10% as a result of the intervention, i.e. 40% in total. This estimate is exploratory and, given the lack of data, rather conservative.

To calculate the sample size for the cluster randomized crossover trial, we used the Shiny CRT Calculator program [57, 58]. Our estimate for the intra-cluster correlation (ICC) is based on results from a study using GPI routine data for various medical indications (*n* = 653,081) [59]. In this study, researchers developed a risk adjustment strategy to improve the use of return to work as a quality indicator for medical rehabilitation. The ICC for the rehabilitation department level (i.e. indications) averages 1.95% (0.0195).

For six cooperating facilities (clusters), a sample size of 29 participants per cluster (clinic) and time period (intervention/control phase; see Fig. 1) is calculated with a power of 0.8 to demonstrate a small intervention effect, i.e. 174 persons for both the intervention and control conditions (total *n* = 348).

We calculated an expected dropout of approximately 35% from T1 to T2. Due to a lack of data from comparable studies, we used willingness to participate in various medical rehabilitation or aftercare studies as a proxy for willingness to participate in the follow-up consultation [23, 60–68]. Willingness to participate in these studies ranged between 42% and 85% (mean: 67%). Moreover, presumably not all study participants will take part in the follow-up consultation and its use is also contingent upon the participation of the respective GPs. On this basis, we assume a realistic dropout rate of 35%.

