From T2 to T3, a further dropout of approximately 20% can be assumed. Data from various rehabilitation studies with 3- or 6-month follow-ups show dropout rates ranging between 5% and 28%, with an average of 14% [30, 32, 65, 69–76]. A conservative estimate is therefore a dropout of 20%. This increases the required sample size to a total of *N* = 669 individuals (T1) (T2: *n* = 435 due to a dropout rate of 35%).

The aim of the interviews with rehabilitation patients to evaluate the communication aid for patients (Phase 1) is to cover all indications included in the cooperating rehabilitation centers (orthopedics, endocrinology/diabetology, cardiology). We plan to recruit two to three individuals per indication. The objective of the interviews has a defined focus, the sample can be considered specific to the study context, and the interviews are characterized by a high degree of interactivity and dialogue. According to Malterud et al. [77], it can therefore be assumed that the proposed number of participants is sufficient to obtain the desired information for evaluating the communication aid. In addition, this limits the effort required to conduct the interviews (recruiting participants by clinic staff, finding time slots for participants outside their therapy schedules, organizing and securing rooms in the rehabilitation center, travel arrangements for project staff).

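### Multiple imputation depends on the data showing MAR, which observed data cannot show, while the plan expects about 48% loss by T3

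*Protocol article*

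**What the plan says.** The primary outcome is patient-reported use of aftercare at T3, four months after rehabilitation. For its analysis, the section *Statistical methods, data analysis* says that "analysis of variance and related methods (analysis of covariance, regression analysis) will be used". It fixes no covariates for that analysis.

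On missing data, the same section gives a check and then a rule. The check: "we will perform subgroup analyses comparing complete datasets with those containing missing data". The rule: "If the missing data shows to be Missing At Random (MAR), we plan to apply multiple imputation techniques to increase the statistical power". The sentence goes on to name robustness as a second aim. Nothing is said about what is done if MAR is judged not to hold.

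The section *Sample size, Rehabilitation patients* sets the expected losses. "We calculated an expected dropout of approximately 35% from T1 to T2". The basis for this figure is "willingness to participate in various medical rehabilitation or aftercare studies as a proxy for willingness to participate in the follow-up consultation". Then: "From T2 to T3, a further dropout of approximately 20% can be assumed". Table 1 shows that the T2 questionnaire goes to the intervention group only.

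**The concern.** The rule asks the data to settle something they hold no information about. MAR says that, given what was observed, missingness does not depend on the unobserved value. MNAR says that it still does. Two mechanisms, one of each kind, can produce identical observed records, so no comparison of completers with non-completers can choose between them. It can only count against MCAR.

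Two things follow. First, the condition can never properly be met. A team that finds differences at T1 could call this MAR and impute, or call MAR not shown and leave the outcomes unimputed. Either way, the form of the primary estimate is chosen after the data are seen. Second, no step in the stated rule addresses MNAR, although the outcome is self-reported and aftercare motivation could plausibly drive both aftercare use and return of the questionnaire.

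At stake is how far the primary result can be trusted when about half of the recruited patients are expected to lack the primary outcome.

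**Working it through.** **Step 1: the plan's own loss figures.** Inputs from the sample size section: 348 patients needed at T3, 20% loss from T2 to T3, 35% loss from T1 to T2.

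- T2: 348 / (1 - 0.20) = 435, as stated.
- T1: 435 / (1 - 0.35) = 669.2, stated as 669.
- Cumulative loss: 1 - 0.65 × 0.80 = 0.48. Check: 1 - 348/669 = 0.4798, that is 669 - 348 = 321 patients without a T3 outcome.

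**Step 2: what the observed data cannot tell.** Use the planning rates (30% control, 40% intervention) as the rates seen among the 52% who respond in each group. True difference = 0.52 × (responder difference) + 0.48 × (non-responder difference).

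| Assumed use in non-responders (intervention / control) | Calculation | True difference |
|---|---|---|
| 40% / 30% | 0.52 × 10 + 0.48 × 10 | 10.0 points |
| 30% / 30% | 0.52 × 10 + 0.48 × 0 | 5.2 points |
| 20% / 30% | 0.52 × 10 + 0.48 × (-10) | 0.4 points |

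The observed T3 outcomes are the same in all three rows, and nothing prevents the T1 records from being the same too. A comparison of complete with incomplete records would then read identically each time. With no assumption about non-responders, the difference could lie anywhere from 0.52 × 0.40 - (0.52 × 0.30 + 0.48) = -42.8 points to (0.52 × 0.40 + 0.48) - 0.52 × 0.30 = +53.2 points. The range is wide because 48% is missing. An assumption has to do the work, so it should be stated in advance.

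**Step 3: what the choice of method can do under MAR (illustration only).** None of these settings comes from the documents except N = 669 and the 30% and 40% rates. The assumed settings are 48% missing in each group, no clustering, one T1 covariate that predicts use (log odds ratio 1.0 per SD), and response that depends on that covariate with log odds ratio 0.8 per SD where stated. There were 1,500 simulated trials with 10 imputations each, and the true difference is 10 points.

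| Response depends on the covariate | Unadjusted complete cases | Imputation using the covariate |
|---|---|---|
| not at all (MCAR) | 10.0 | 9.9 |
| equally in both groups | 10.7 | 9.9 |
| in the intervention group only | 16.4 | 9.8 |

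The imputation model contains the one variable that drives response, so this setting favours imputation by construction. The table shows that an unadjusted complete-case comparison relies on more than MAR. It does not estimate bias in this trial.

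**The case against.** The strongest reply is that this is loose wording, and that the handling of a rejected MAR assumption belongs in an analysis plan that is not shown. The second half stands: silence on the fallback, the imputation variables or a sensitivity grid is not in itself a fault in an article. But the condition is stated in the article, and an analysis plan that follows it would inherit the fault.

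Four stronger readings are tempting, and the documents do not support them.

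- *The rule leads to a complete-case primary result.* A reader might infer this because nothing else is named. The article does not say it, and imputing after finding T1 differences is at least as natural an outcome.
- *Complete cases always need stronger assumptions.* That holds for an unadjusted comparison. The article also names analysis of covariance and regression. When only the outcome is missing, a complete-case regression adjusted for the predictors of missingness needs about the same assumption as imputation with those variables.
- *Losses differ by group and bias the effect by a known amount.* With 52% response in the intervention group, 80% in controls and a 15-point gap between responders and non-responders, all assumed, the overstatement would be 0.48 × 15 - 0.20 × 15 = 4.2 points. The plan applies both losses to the whole sample, so it does not foresee those rates. With equal groups they would also mean (48 + 20)/2 = 34% overall loss, not 48%. With equal response and the same gap in both groups, the result is 7.2 - 7.2 = 0. If T1 variables do not explain the gap, imputation under MAR would not remove it either.
- *The power rationale is wrong.* The sentence also names robustness. Imputation can keep records with missing covariates or moderators and can gain some precision from auxiliary data. There is no case for striking the phrase.

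**Conclusion.** The point holds in a limited form. Imputation is tied to a condition that the described check cannot establish, so whether the primary estimate is imputed would be decided after the data are seen. This rests on the article's stated rule and on the fact that MAR and MNAR cannot be told apart from observed data.

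Its weight comes from the planned 48% loss, 321 of 669. That is a planning figure. The 35% part stands in for willingness to attend a consultation that controls are not offered, and the *Recruitment* section does not say that patients who miss T2 receive no T3 questionnaire. Actual loss at T3 may be lower. It could also differ between groups, because only the intervention group has a T2 stage, but the documents do not establish that it will.

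The size of any bias cannot be derived from the documents. The change is worth making before outcomes are analysed.

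**What to change.** 1. Drop the condition. State MAR, given named variables, as an assumption of the primary analysis.
2. Pre-specify one primary approach: multiple imputation, or a covariate-adjusted likelihood model. Include condition, clinic, period and T1 predictors such as aftercare recommendation, motivation, self-efficacy, WAS, age and sex. Table 1 shows that the T1 measures are collected in both groups.
3. Keep the comparison of patients with and without T3 data, by condition, as description only. It should not decide the method.
4. Report complete cases as a sensitivity analysis. If the adjusted likelihood model is primary, the informative contrast is the version without the T1 predictors.
5. Add a delta-adjusted (MNAR) analysis that lowers assumed use among non-responders, for example by 0, 5, 10 and 15 points, varied separately by condition, and report where the conclusion would change.

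The cost is a few sentences and modest extra programming. No new data are needed, and the recruitment target of 669 is unaffected by this point.
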